**Data selection criteria for Analysis:**

Unless otherwise stated, for baseline we have to use ASHA screening (ASHA screening 1 and ASHA follow-up 1) data. At post intervention we have to use Post intervention data collected by study interviewers linked with patient ID of ASHA screen positive data.

For certain tables the information at baseline may not be collected by ASHA during their screening. For all such instance, Baseline data collected by study interviewers will be used linked with patient ID of ASHA screen positive data.

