**Smart mental health Final Statistical Analysis plan Primary Analysis:**

The primary objective of the study is:-

To see the difference in anxiety and depression score and health service utilization among the mental health screen positive subject post intervention.

The screen positive subjects at baseline will be looked for their past history for mental health service utilization. The subjects who responded "Yes" against question number 56 "Did you get treated for that mental disorder?" are proportion of subject at baseline who used mental health service.

At post intervention, the number of subjects used health service can be taken from Doctors follow-up data.

The count and percentage will be provided for the subjects who are screen positive for utilization of health services. Proportion of mental health service utilization at baseline and post intervention among the screen positive subject will be statistically analyze by McNemar test. The P-value for comparison of will be presented in same table.

A separate table will be provided for subjects screen positive subjects who actually visited doctor for their treatment at time of intervention. The count and percent by visit will be provided for this.

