### **Statistical Analysis of KAB and BACE:**

For every question related to KAB and BACE, the count and percentage will be presented for every response for the concern question.

Further to that for every question, mean score and SD along with number of people responded to different questions of KAB and BACE will be presented. The difference in score between baseline and post intervention will also be analysed by t-test. The mean SD and the number of people responded at both visit along with p-value will be presented.

For KAB the Total Behaviors SCORE (Except First Question) and For BACE, the Total BACE Score, will also be analyzed and summarized in similar fashion.

A separate table for BACE will be presented for % reporting barrier to any degree and % reporting as a major barrier along with their rank for highest proportion rating as a major barrier. The difference in proportion for %reported a major barrier will be analysed by two- proportion z-test and corresponding p-value will be presented.

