| Not wanting a mental health problem to be on my medical records                                             | xx, xx.xx(xx.xxx)       | xx, xx.xx(xx.xxx)                | xx, xx.xx(xx.xxx) 0.xxxx                          |
| Concern that my children may be taken in to care or that I may lose access
or custody without my consent | xx, xx.xx(xx.xxx)       | xx, xx.xx(xx.xxx)                | xx, xx.xx(xx.xxx) 0.xxxx                          |
| Concern about what my friends might think, say or do                                                        | xx, xx.xx(xx.xxx)       | xx, xx.xx(xx.xxx)                | xx, xx.xx(xx.xxx) 0.xxxx                          |
| Concern about what people at work might think, say or do                                                    | xx, xx.xx(xx.xxx)       | xx, xx.xx(xx.xxx)                | xx, xx.xx(xx.xxx) 0.xxxx                          |
| Overall BACE score                                                                                          | xx, xx.xx(xx.xxx)       | xx, xx.xx(xx.xxx)                | xx, xx.xx(xx.xxx) 0.xxxx                          |

*\*P value is calculated using t-test. BACE=barrier to access care evaluation-Treatment Stigma Subscale. For mean of difference, Subject who have responded to both the visit, have been considered for summary.*

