**Table 6: Percentage reporting and ranks for each barrier in the BACE ASHA screen positive**

| Question                                                                                                | -----Baseline-----                     |                                           |             | -----Post Intervention-----            |                                           |             | * P-Value
Visit 2-3 |
|---------------------------------------------------------------------------------------------------------|----------------------------------------|-------------------------------------------|-------------|----------------------------------------|-------------------------------------------|-------------|------------------------|
|                                                                                                         | %reporting
barrier to
any degree | %reporting as
major
barrier (a lot) | ***
Rank | %reporting
barrier to
any degree | %reporting as
major
barrier (a lot) | ***
Rank |                        |
| Concern that I might be seen as weak for having a mental health problem                                 | xx.xx                                  | xx.xx                                     | x           | xx.xx                                  | xx.xx                                     | x           | 0.xxx                  |
| Concern that it might harm my chances when applying for jobs                                            | xx.xx                                  | xx.xx                                     | x           | xx.xx                                  | xx.xx                                     | x           | 0.xxx                  |
| Concern about what my family might think, say, do or feel                                               | xx.xx                                  | xx.xx                                     | x           | xx.xx                                  | xx.xx                                     | x           | 0.xxx                  |
| Feeling embarrassed or ashamed                                                                          | xx.xx                                  | xx.xx                                     | x           | xx.xx                                  | xx.xx                                     | x           | 0.xxx                  |

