| Concern about what people at work might think, say or do                                                | xx.xx                                  | xx.xx                                     | x           | xx.xx                                  | xx.xx                                     | x           | 0.xxx                  |
| Overall Mean                                                                                            | xx.xx                                  | xx.xx                                     | x           | xx.xx                                  | xx.xx                                     | x           | 0.xxx                  |

\* *P-value calculated based on difference in proportion reported as major barrier.*

\*\*\* *Rank (1=item has highest proportion rating as a major barrier)*

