| Did you take medicines as prescribed by the primary care doctor on a regular basis? | xx(xx.xx)                |

*N=Total no. of patients in Baseline; n=No. of patients in particular category*

Table 15: Summary of for Utilization of Health Services for Screen Positive subjects

| Screen Positive | Health Service used ** | Baseline
(N=xxxxx)
n (%) | Post Intervention
(N=xxxxx)
n (%) | P-value |
|-----------------|------------------------|--------------------------------|-----------------------------------------|---------|
| By ASHA         | Yes                    | xxx (xx.xx)                    | xxx (xx.xx)                             | 0.xxxx  |
|                 | No                     | xxx (xx.xx)                    | xxx (xx.xx)                             |         |
| By Interviewer* | No                     | xxx (xx.xx)                    | xxx (xx.xx)                             | 0.xxxx  |
|                 | Yes                    | xxx (xx.xx)                    | xxx (xx.xx)                             |         |

\* This includes only those patients who were screen positive by Study Interviewer but not by ASHA.

\*\* Health Service used: At baseline: Response from the question "Did you get treated for that mental disorder?"

At Post Intervention: Response from the question "Did you get treated for your mental health condition as indicated by ASHA/Interviewer?"

P-Value is calculated based on Mc-nimar test for matched pair test of proportion.

Table 16a: Case control analysis of Change in Depression/Anxiety Score from Baseline to Post Intervention for those who had a score  $\geq 10$  at the beginning of the intervention.

| Category   | Type    | Statistics | Baseline     | Post Intervention | Change       | P-Value for difference |
|------------|---------|------------|--------------|-------------------|--------------|------------------------|
| Anxiety    | Cases   | N          | xxxxx        | xxxxx             | xxxxx        | 0.xxxx                 |
|            |         | Mean (SD)  | xx.x (xx.xx) | xx.x (xx.xx)      | xx.x (xx.xx) |                        |
|            |         | Median     | xx.x         | xx.x              | xx.x         |                        |
|            |         | Min, Max   | xx; xx       | xx; xx            | xx; xx       |                        |
|            | Control | N          | xxxxx        | xxxxx             | xxxxx        |                        |

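### Table 6 of the SAP tests before/after change in the 12 BACE items with an unpaired two-proportion z-test, although the visits are linked by patient ID and the test's independence assumption fails

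*SAP*

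**What the plan says.** The SAP section on the statistical analysis of KAB and BACE fixes the test for Table 6: "The difference in proportion for %reported a major barrier will be analysed by two- proportion z-test". The Table 6 footnote repeats the target without naming a test: "P-value calculated based on difference in proportion reported as major barrier". The table prints one p-value for each of 12 barrier items, plus an overall row.

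The population is the ASHA screen positives, as the table title shows: "Percentage reporting and ranks for each barrier in the BACE ASHA screen positive". The section on data selection criteria ties both visits to the same patient ID. For the later visit: "At post intervention we have to use Post intervention data collected by study interviewers linked with patient ID of ASHA screen positive data". For baseline items that the ASHAs did not collect: "Baseline data collected by study interviewers will be used linked with patient ID of ASHA screen positive data".

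Two other places treat such data as paired:
- Table 5 reports post-minus-baseline change on the same 12 items, and its footnote says: "Subject who have responded to both the visit, have been considered for summary".
- For service use, the primary analysis section says: "Proportion of mental health service utilization at baseline and post intervention among the screen positive subject will be statistically analyze by McNemar test". The Table 15 footnote gives the reason: "P-Value is calculated based on Mc-nimar test for matched pair test of proportion".

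**The concern.** A two-proportion z-test takes the variance of the difference as the sum of two separate variances. When the same people answer the same question twice, a covariance term belongs in that variance, and this test omits it. The result is a p-value calibrated for a design that the SAP does not have.

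The SAP reserves its other independent-sample tests for cases against controls, who are different people. Table 6 is the one before/after proportion given an unpaired test, and nothing in the document justifies the exception. What is at stake is whether a reader can trust the 12 item p-values as evidence of change in treatment-stigma barriers.

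**Working it through.** The SAP gives no sample size, BACE rates, significance level or correlation, so it has no figure to reproduce. The inputs below are assumptions, shown over a range. Tests are two-sided at 5%.

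**1. Variance ratio.** Let p be the common proportion under the null, n the number answering at each visit, rho the within-person correlation of the yes/no answer, and f the fraction of subjects seen at both visits (equal-sized samples).
- Variance assumed by the z-test: 2p(1−p)/n.
- True variance: 2p(1−p)(1−f·rho)/n.
- Ratio, true to assumed: 1−f·rho, which equals 1−rho with full pairing.

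**2. True size.** Size = 2 × [1 − Φ(1.96/√(1−f·rho))].

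| Overlap f | rho 0.1 | rho 0.3 | rho 0.5 |
|---|---|---|---|
| 100% | 3.9% | 1.9% | 0.6% |
| 80% | 4.1% | 2.5% | 1.1% |
| 50% | 4.4% | 3.4% | 2.4% |

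For example, with full pairing and rho 0.3, 1.96/√0.7 = 2.343, which gives 1.9%. Simulation (200 pairs, p = 20%, 200,000 runs) gave 4.0%, 2.0% and 0.6% for the z-test at the three correlations, and 5.0% to 5.2% for McNemar. At rho = 0 the z-test is correct (5.1% simulated). At rho = −0.1 its size is 6.2%, so the p-values are then too small.

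**3. One illustrative table, full pairing.** Take 400 pairs, with *a lot* falling from 100 to 80; 50 subjects change one way and 30 the other.
- Unpaired: pooled p = 0.225; SE = √(2 × 0.225 × 0.775/400) = 0.0295; z = 0.05/0.0295 = 1.69; p = 0.090.
- McNemar: (50−30)²/(50+30) = 5.0; p = 0.025.

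The implied correlation is (0.125 − 0.25 × 0.20)/√(0.25 × 0.75 × 0.20 × 0.80) = 0.43. The numbers are invented and fall on either side of 0.05. They show the mechanism, not an expected result.

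**4. Power with full pairing.** For 20% falling to 14% in 200 pairs, power of the z-test against McNemar is 36% v 39%, 34% v 48% and 31% v 63% at rho 0.1, 0.3 and 0.5. At 900 pairs and rho 0.3 it is 96% v 98%, so the loss is small in a large sample.

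**5. Power with partial overlap.** For 25% falling to 19%, 400 answering at each visit, 50% overlap (200 pairs) and rho 0.1:
- z-test: 0.06/√(2 × 0.22 × 0.78/400) = 2.05; power about 54%.
- McNemar on pairs: the joint proportion is 0.25 × 0.19 + 0.1 × √(0.25 × 0.75 × 0.19 × 0.81) = 0.0645, so the discordant proportions are 0.1855 and 0.1255; 0.06 × √200/√0.311 = 1.52; power about 33%.

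In simulations of the same case, McNemar has 33%, 40% and 54% power at rho 0.1, 0.3 and 0.5 with 50% overlap, against 54% for the z-test. With 70% overlap McNemar has 44%, 54% and 68%, against 54% to 55%.

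**The case against.** The strongest objection is that full pairing is assumed, not shown. The visit schedule section says that post-stigma records are appended to the post-intervention data set. Every BACE item offers an NA response. Table 6, unlike Table 5, is not limited to subjects seen at both visits. This stands as a limit on size: overlap may be partial, and the distortion shrinks with it. It does not rescue the test, because partly overlapping samples are not independent either.

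Four stronger readings are tempting, and the documents do not support them.
- A reader might infer that the p-values are certainly too large and that real falls in barriers will be missed. That needs positive correlation and substantial overlap, and the SAP states neither. Step 5 shows that with partial overlap a pairs-only McNemar test can have less power than the planned test. The case for a paired test rests on validity, not on a guaranteed gain in power.
- A reader might take the p-value column header *Visit 2-3* to mean that the comparison is undefined. The visit schedule section sets baseline against post intervention as the default, and Table 6 has exactly those columns. The header is a stray label.
- A reader might expect Tables 5 and 6 to agree once both are paired. Table 5 tests a mean score and Table 6 the single answer *a lot*, so they can still differ.
- A reader might conclude that Tables 3 and 5 are also unpaired because their footnotes say only t-test. Both already restrict the difference to subjects who responded at both visits, so adding the word *paired* would only clarify.

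**Conclusion.** The mismatch between design and test is established from the SAP alone: linked subjects, an independent-samples test, and the appropriate matched-pair test already used elsewhere in the same document. The standard error for the 12 item rows is wrong unless the within-person correlation is zero or no subject answered at both visits.

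Direction and size are conditional. Positive correlation is the natural expectation when one person answers the same item twice, and it makes the test conservative to the extent shown in the table of true sizes.

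Severity is moderate. The primary objective concerns symptom scores and service use, BACE lies outside it, and the likely error does not manufacture false claims of benefit. The point does not cover the *Overall Mean* row, which is not a single proportion.

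**What to change.** In the KAB and BACE analysis section, and in the Table 6 footnote, replace the two-proportion z-test for the 12 item rows with McNemar's test on subjects who answered the item at both visits, using the exact form if discordant pairs are few. Print the number of pairs for each item. Relabel the *Visit 2-3* column as Baseline vs Post Intervention.

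The cost is a wording change in the text and the table shell and one programming change. The percentages and ranks stay as planned.

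The downside is that single-visit responders leave the p-value. If there are many of them, specify instead a z-test whose variance subtracts the covariance from the overlapping subjects. With n1 and n2 responders and m pairs, the variance is p1(1−p1)/n1 + p2(1−p2)/n2 − 2m·cov/(n1·n2), where cov is estimated from the pairs. This keeps all responders and is valid, provided that single-visit responders come from the same population as the pairs. Choose between the two from the counts of pairs and single-visit responders, before any p-value is seen.

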### **Stressful events:**

The count and percentage will be provided for the screen positive subjects for the questions of stressful events for which they responded as yes at baseline.

A separate table will be provided for the questions of stressful events for which they responded as yes for the subjects who had Depression or Anxiety Score  $\geq 10$ .

The stressful events will be summarized in 4 categories (0, 1, 2-3,  $\geq 4$ ) by count and percentage. Also Descriptive Statistics (n, mean, SD, Min, and Max) for the patients who have total score greater than 1 will be provided.

### **Sharing personal problems:**

The count and percentage will be provided for those subjects who had responded yes for the Question "When you have a personal problem do you share it with anyone?" at baseline.

### **Assessment of Alcohol and substance use:**

The count and percentage will be provided for those subjects who had responded yes for all the 10 different questions of alcohol and substance use section.

### **Past history of illness:**

The count and percentage will be provided for those subjects who had responded yes for the questions of heart attack or angina or stroke or diabetes or cancer.

The count and percentage will be provided separately for those subjects who had responded yes for the questions of mental disorder with count and percentage for those subjects who had responded yes for the questions "Did you get treated for that mental disorder?" in similar fashion.

### **Subject referral by ASHA and PHC doctors:**

The count and percentage will be provided for those subjects who were referred by ASHA to PHC doctor during intervention and among all such screen positive subjects again count and percentage will be provided for those subjects who were referred by PHC doctor for more specialized care.

**Table1: Demographic and Socioeconomic characteristics**

| Characteristics     | Baseline
(N=XX)
n% | Post Intervention
(N=XX)
n% |
|----------------------------|-----------------------------------|--------------------------------------------|
| Gender              |                                   |                                            |
| Female                     | xx(xx.x%)                         | xx(xx.x%)                                  |
| Male                       | xx(xx.x%)                         | xx(xx.x%)                                  |
| Occupation          |                                   |                                            |
| Housewife/Retired          | xx(xx.x%)                         | xx(xx.x%)                                  |
| Organized Sector           | xx(xx.x%)                         | xx(xx.x%)                                  |
| Other                      | xx(xx.x%)                         | xx(xx.x%)                                  |
| Unorganized Sector         | xx(xx.x%)                         | xx(xx.x%)                                  |
| Education           |                                   |                                            |
| Graduate/Postgraduate      | xx(xx.x%)                         | xx(xx.x%)                                  |
| High School                | xx(xx.x%)                         | xx(xx.x%)                                  |
| No School                  | xx(xx.x%)                         | xx(xx.x%)                                  |
| Other                      | xx(xx.x%)                         | xx(xx.x%)                                  |
| Primary School             | xx(xx.x%)                         | xx(xx.x%)                                  |
| Marital Status      |                                   |                                            |
| Currently Married          | xx(xx.x%)                         | xx(xx.x%)                                  |
| Never Married              | xx(xx.x%)                         | xx(xx.x%)                                  |
| Separated/Divorced/Widowed | xx(xx.x%)                         | xx(xx.x%)                                  |
| Age(Years)          |                                   |                                            |
| Mean(SD)                   | xx.xx(xx.xxx)                     | xx.xx(xx.xxx)                              |
| Range                      | xx.x; xx.x                        | xx.x; xx.x                                 |

*N=Total no. of patients in that visit. n= No. of patients with particular characteristic.*

**Table 2: Summary for KAB**

|          | Question                                                                                                                           | Baseline
(N=XX)
n% | Post Intervention
(N=XX)
n% |
|----------|------------------------------------------------------------------------------------------------------------------------------------|--------------------------|-----------------------------------|
| Context* | Have you seen or heard any information about mental health or mental illness issues in the last year, in any of these ways? |                          |                                   |
|          | [Newspaper/TV]                                                                                                                     | xx(xx.x%)                | xx(xx.x%)                         |
|          | [Other]                                                                                                                            | xx(xx.x%)                | xx(xx.x%)                         |
|          | [People talking about it/ Other]                                                                                                   | xx(xx.x%)                | xx(xx.x%)                         |
|          | [People talking about it]                                                                                                          | xx(xx.x%)                | xx(xx.x%)                         |
|          | [TV/Health center/People talking about it / Other]                                                                                 | xx(xx.x%)                | xx(xx.x%)                         |
|          | [TV/ Other]                                                                                                                        | xx(xx.x%)                | xx(xx.x%)                         |
|          | [TV/People talking about it/ Other]                                                                                                | xx(xx.x%)                | xx(xx.x%)                         |
|          | [TV]                                                                                                                               | xx(xx.x%)                | xx(xx.x%)                         |
|          | Where do people in this community first go to seek care for mental illness?                                                 |                          |                                   |
|          | [Hospital]                                                                                                                         | xx(xx.x%)                | xx(xx.x%)                         |
|          | [Local clinic]                                                                                                                     | xx(xx.x%)                | xx(xx.x%)                         |
|          | [Neighbor/ Community Member]                                                                                                       | xx(xx.x%)                | xx(xx.x%)                         |
|          | [Nowhere/ Care is not available]                                                                                                   | xx(xx.x%)                | xx(xx.x%)                         |
|          | [Other]                                                                                                                            | xx(xx.x%)                | xx(xx.x%)                         |
|          | [Religious or spiritual advisor]                                                                                                   | xx(xx.x%)                | xx(xx.x%)                         |
|          | [Traditional healer]                                                                                                               | xx(xx.x%)                | xx(xx.x%)                         |

|                                                                       |                                                                    |           |           |
|-----------------------------------------------------------------------|--------------------------------------------------------------------|-----------|-----------|
| Do any of the following people you know have a mental illness? |                                                                    |           |           |
|                                                                       | [Family member in this household]                                  | xx(xx.x%) | xx(xx.x%) |
|                                                                       | [Family member outside this household]                             | xx(xx.x%) | xx(xx.x%) |
|                                                                       | [Friends/Acquaintance]                                             | xx(xx.x%) | xx(xx.x%) |
|                                                                       | [Neighbor]                                                         | xx(xx.x%) | xx(xx.x%) |
|                                                                       | [No one known]                                                     | xx(xx.x%) | xx(xx.x%) |
|                                                                       | [Someone else]                                                     | xx(xx.x%) | xx(xx.x%) |
| Knowledge                                                      | Mentally ill people tend to be violent                      |           |           |
|                                                                       | Agree Slightly                                                     | xx(xx.x%) | xx(xx.x%) |
|                                                                       | Agree Strongly                                                     | xx(xx.x%) | xx(xx.x%) |
|                                                                       | Disagree Slightly                                                  | xx(xx.x%) | xx(xx.x%) |
|                                                                       | Disagree Strongly                                                  | xx(xx.x%) | xx(xx.x%) |
|                                                                       | Don't know                                                         | xx(xx.x%) | xx(xx.x%) |
|                                                                       | Neither agree or disagree                                          | xx(xx.x%) | xx(xx.x%) |
|                                                                       | People with mental illness can't live a good rewarding life |           |           |
|                                                                       | Agree Slightly                                                     | xx(xx.x%) | xx(xx.x%) |
|                                                                       | Agree Strongly                                                     | xx(xx.x%) | xx(xx.x%) |
|                                                                       | Disagree Slightly                                                  | xx(xx.x%) | xx(xx.x%) |
|                                                                       | Disagree Strongly                                                  | xx(xx.x%) | xx(xx.x%) |
|                                                                       | Don't know                                                         | xx(xx.x%) | xx(xx.x%) |
|                                                                       | Neither agree or disagree                                          | xx(xx.x%) | xx(xx.x%) |

